## Background

Gliomas represent the most common type of primary brain tumors and are frequently associated with clinical symptoms including seizures [1–7]. The majority of patients with high-grade gliomas (grade III or IV according to the classification of the World Health Organization) receive radiotherapy with or without chemotherapy, either as adjuvant treatment after neurosurgical resection or as definitive treatment after biopsy. Due to an acute inflammatory reaction associated with edema in the irradiated area of the brain and subsequent increase of intracranial pressure, radiotherapy may lead to onset or progression of clinical symptoms including seizures during the course of treatment [8, 9]. To our knowledge, no studies are available that focused on the subacute effect of radiotherapy on seizure activity during a course of radiation treatment in glioma patients. These data would be important to improve monitoring and anti-epileptic treatment of these patients. This study evaluates the seizure activity during radiotherapy for high-grade (grade III or IV) gliomas.

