### Assessments

Parameters assessed prior radiotherapy include demographics (age, date of birth, gender), medical history, concomitant diseases, concomitant medication including anti-epileptic treatment, physical examination, histology and grade of glioma, upfront surgery, and planned radiotherapy/radio-chemotherapy.

The following parameters will be assessed during the trial (Fig. 1):
Seizure frequency

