### Electroencephalography (EEG)

The patients receive an EEG during the first and the sixth week of radiotherapy, as well as during the sixth week following radiotherapy. Activity typical for epilepsy includes spike waves, sharp waves and/or sharp slow waves and is classified as absent or present.

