## Sample size calculations

The main goal of the study is to generate objective data on the occurrence, frequency and severity of seizures and the use of anti-epileptic medication during the course of radiotherapy applying standardized questionnaires, in order to evaluate the potential effect of radiotherapy in patients with high-grade gliomas and generate hypotheses. Thirty-two patients are required for the statistical analyses. Assuming that 10% of patients do not fulfil these requirements, a total of 35 patients should be enrolled to this trial. With this sample size, a one-sample binomial test with a one-sided significance level of 2.5% has a power of 80% to yield statistical significance if the rate of patients with progression of seizure events during the course of radiotherapy is 30% (rate under the alternative hypothesis), assuming a ‘natural’ background progression-rate of 10% without radiotherapy (null hypothesis). The latter rate was chosen after discussions with experienced neurologists. If the natural course of the disease would lead to a progression-rate of 5% without radiotherapy, the power increases to 98%. Recruitment should be completed within 12 months. The radiotherapy period is 6–6.5 weeks, and follow up is 6 weeks. Thus, duration of the trial is about 15 months.

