In order to describe the time profiles of seizure frequencies in more detail, normalized seizure frequencies over time will be calculated within 3-week intervals, namely weeks 1–3 and 4–6 during radiotherapy, and weeks 1–3 (7–9 in total) and 4–6 (10–12 in total) following radiotherapy. These frequencies will be subjected to descriptive statistics as well as graphical presentations by means of box-and whisker diagrams. For exploratory purposes, the Wilcoxon signed-rank test will be applied to compare the two-time windows during the course of radiotherapy; the Friedman-Test will be applied to assess whether there is any difference in seizure frequencies between all of the time intervals during the course of radiotherapy and thereafter.

In addition, the percent change from baseline in seizure frequency will be considered and subjected to descriptive analysis. For further exploratory analysis, the rates of patients experiencing any seizure (yes/no) at baseline and at each time interval will be estimated together with their associated confidence intervals. Subsequent analyses focus on the clinically relevant generalized seizures only.

Patient satisfaction with the seizure diary will be assessed at the end of radiotherapy using a questionnaire and subjected to descriptive analysis. In case of a dissatisfaction rate > 40%, the seizure diary will be considered not suitable for patients with high-grade gliomas. EEG activity typical for epilepsy will be performed during the first and sixth week of radiotherapy, and the sixth week following radiotherapy. EEG activity typical for epilepsy is classified as absent or present. Statistical analysis is focused on data description only. A mean change to baseline (during first week of radiotherapy) by 50% regarding the number of patients with EEG activity typical for epilepsy will be considered clinically relevant.

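### The EEG has no pre-treatment reference, and the 50% relevance rule built on it states neither direction nor precision (minor)

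*Protocol article*

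**What the plan says.** The section on electroencephalography sets three recordings: "The patients receive an EEG during the first and the sixth week of radiotherapy, as well as during the sixth week following radiotherapy". The Assessments section gives the same schedule and presents the EEG as an objective complement to the patient-reported diary. It is the only such measure the article describes.

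The list of assessments before treatment ("Parameters assessed prior radiotherapy include demographics (age, date of birth, gender), medical history, concomitant diseases, concomitant medication including anti-epileptic treatment", followed by examination, histology, surgery and planned treatment) contains no EEG.

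In the statistical methods section the result is binary ("EEG activity typical for epilepsy is classified as absent or present"), and the analysis is described thus: "Statistical analysis is focused on data description only". The next sentence nevertheless sets a benchmark for clinical relevance: "A mean change to baseline (during first week of radiotherapy) by 50% regarding the number of patients with EEG activity typical for epilepsy". No direction, interval or expected number of EEG-positive patients is given, and it is not said which of the two later EEGs the benchmark applies to.

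**The concern.** The Background gives the reason for the trial as worsening of symptoms during treatment: "Due to an acute inflammatory reaction associated with edema in the irradiated area of the brain", with a subsequent rise in intracranial pressure. If that is the hypothesis, the reference should precede irradiation. A reference taken on treatment absorbs whatever has already happened and pulls the EEG contrast towards no change. Because the week is fixed but not the position relative to the first fractions, patients may also differ in how much irradiation precedes their reference EEG.

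The benchmark raises a separate problem. It is a relative change in a count taken twice in the same small group. If few patients are positive, one or two changing status can produce a 50% change, and the label of clinical relevance would then attach to sampling variation. The article expects its findings to inform monitoring, anti-epileptic treatment and a larger trial, so the label could carry weight.

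**Working it through.** **1. Timing, from the text.** The Assessments section, the EEG section and the statistical methods section all place the first EEG in radiotherapy week 1, and the last of these names it as baseline. The pre-radiotherapy list has no EEG. The on-treatment reference is therefore the stated design, not a detail lost in condensing the protocol. How much effect it absorbs cannot be computed, because neither the day within week 1 nor the speed of onset is given.

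**2. The plan's own figures.** There are none for the EEG rule. The sample size statement ("Thirty-two patients are required for the statistical analyses") supplies n = 32. Its power claims reproduce with the exact binomial test. Against 10%, rejection at 8 or more has one-sided level 1.17% and power 78.8% at a true 30% (stated: 80%). Against 5%, rejection at 5 or more has level 2.04% and power 98.1% (stated: 98%). Neither says anything about the EEG.

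**3. How often the 50% rule is met with no true change.**

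Inputs:
- n = 32, from the sample size section.
- EEG-positive rate p: **assumed**. The Discussion gives the centre's own pre-radiotherapy *seizure* prevalence as 21.5% (grade IV) and 48.8% (grade III). These are used as imperfect proxies, about 7 and 16 of 32. The values 10% and 30% are added to show the range.
- Within-patient correlation ρ between two EEGs: **assumed**, 0.3 to 0.7.

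Model, with the same p at both visits:
- P(positive later | positive at baseline) = a = p + ρ(1 − p)
- P(positive later | negative at baseline) = b = p(1 − ρ)
- N₁ ~ Bin(32, p); given N₁ = k, N₂ is the sum of Bin(k, a) and Bin(32 − k, b)
- The rule is met if N₂ ≥ 1.5·N₁ or N₂ ≤ 0.5·N₁, summed exactly over N₁ ≥ 1

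Example, p = 0.215 and ρ = 0.5: a = 0.215 + 0.5 × 0.785 = 0.6075; b = 0.215 × 0.5 = 0.1075. A rise of 50% or more has probability 14.7% and a fall of 50% or more 5.0%, together 19.7%.

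| Positive rate p | Expected positive of 32 | Either direction, ρ = 0.3 | ρ = 0.5 | ρ = 0.7 |
|---|---|---|---|---|
| 10% | 3.2 | 48% | 42% | 31% |
| 21.5% | 6.9 | 26% | 20% | 12% |
| 30% | 9.6 | 16% | 11% | 5% |
| 48.8% | 15.6 | 4% | 2% | 1% |

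The rule is undefined if nobody is positive in week 1. At p = 10% this has probability 0.9³² = 3.4%. The 10% row excludes those trials from the triggers. Counting a rise from zero as a trigger moves 48% to 51% at ρ = 0.3, hence the range of 31–51%. At 21.5% and above the choice makes no visible difference.

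**4. Two follow-up EEGs.** If either later EEG may meet the rule (simulation of 60,000 trials, first-order dependence, ρ = 0.5), the either-direction rates are 63% at 10% positive, 35% at 21.5%, 21% at 30% and 6% at 48.8%.

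**5. A single case.** With 6 positive at baseline, 9 at follow-up meets the rule. Even if nobody changes the other way, the 3 new positives give an exact two-sided McNemar p of 2 × 0.5³ = 0.25. The exact 95% interval for 6/32 alone is 7% to 36%.

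**The case against.** The EEG is secondary and descriptive. The primary composite uses diary frequency, generalized seizures and medication, so the sample size and primary test are untouched. A relevance benchmark is not a significance test, claims no error control, and triggers no stated action, unlike the 40% dissatisfaction rule for the diary. A week-6 versus week-1 contrast still addresses change during most of the course. Leaving out a direction may be deliberate, since the Discussion describes possible worsening during radiotherapy and improvement months later. The choice of table and interval is commonly left to the analysis plan, and the article does not exclude a paired table.

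Most of this stands and sets the severity. It does not remove the point: the article itself fixes the on-treatment reference and attaches a relevance label to a bare count. If both directions were meant, the text should say so.

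Two stronger readings are tempting and are not supported:

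- A reader might infer that the EEG will miss an early effect of radiotherapy. The documents do not place the EEG before or after the first fractions, and nothing in them says that an effect appears within days. Only an effect already present at the recording is absorbed, and its size is unknown.
- A reader might infer that the rule rests on a handful of positive patients and will often be met by chance. The article gives no EEG-positive rate. At the centre's own grade III seizure prevalence, used as a proxy, the rule is met by chance in only 1–4% of trials for one follow-up EEG.

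**Conclusion.** The concern holds in a limited form. The only objective measure of seizure activity described has no pre-treatment reference, and this follows from the text without any assumption; the amount of effect absorbed is unknown. The 50% rule states no direction and no precision, also from the text.

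How much the second defect matters depends on a rate that the documents do not give. For one follow-up EEG, 32 patients and correlation 0.3 to 0.7, chance triggering in either direction is about 31–51% at 10% positive and 12–26% at 21.5%, falling to 5–16% at 30% and 1–4% at 48.8%. It is material if about 20–25% of patients or fewer are positive, and not at the upper end of the range. Lower correlation, or letting either follow-up EEG count, raises these figures; more stable EEG findings lower them. Severity is minor, because no primary inference depends on the EEG.

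**What to change.** 1. Record the first of the three planned EEGs before the first fraction and define that recording as baseline. Keep the other two as scheduled.
2. For each follow-up EEG separately, report the paired table (absent to present, present to absent) and the paired difference in proportions with a 95% interval.
3. Do not call a 50% change in the number of positive patients clinically relevant without that interval. If a benchmark is kept, state its direction and which follow-up EEG it applies to.

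The number of EEGs stays the same. The cost is some scheduling effort before treatment starts; the article does not describe the visits in that period, so how much effort cannot be judged from it. The reporting changes need no additional data.

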## Data management and monitoring

Patients can be identified only by the individual patient number, date of birth and gender. A patient list will be kept at the trial center alone. The data will be pseudonymized prior to analyses and handled in accordance with the General Data Protection Regulation. Originals of the key trial documents will be stored at the contributing center (sponsor’s site) for at least 10 years following the final report. The principal investigator will store administrative documents, the patient list, signed informed consent forms, copies of documentation forms and general documentation. Original patient files must be kept for 30 years according to the German regulations for radioprotection. Initiation of the study and on-site monitoring will be performed by the ZKS Lübeck. Regular audits are not planned but may be performed if considered necessary. Since this trial is not related to the German pharmaceutical or medicinal product act, inspections of higher federal authorities are not scheduled. A data monitoring committee is not necessary, because the patients do receive the same treatment for high-grade glioma as outside this trial. The coordinating investigator will work towards comprehensive dissemination of the study findings. Coordinating investigator, biostatistician and staff members involved in the trial will provide a study report. Study results will be published in a peer-reviewed journal and are planned to be presented at scientific meetings. Publications will be coordinated with and supported by a professional biostatistician. For publications the acronym SURF-ROGG will be used. Data analysts and statisticians are blinded.

## Discussion

Primary brain tumors such as gliomas can be associated with seizures. For patients with grade III or IV gliomas, pre-treatment seizure rates of 29–67% and 9–45%, respectively, were reported [3, 15–19]. Moreover, in a study from our group, the prevalence of seizures prior to radiotherapy was 48.8% in patients with grade III gliomas and 21.5% in patients with grade IV gliomas, respectively [14].

Radiotherapy improves long-term seizure outcomes in glioma patients. In a retrospective study of 43 patients with diffuse gliomas (33 patients with a grade II glioma and 10 patients with a grade III glioma), seizure reduction of ≥50% compared to baseline was observed in 31 patients (72%) at 3 months following radiotherapy [20]. Moreover, in a randomized trial comparing early radiotherapy with 54 Gy in 30 fractions to radiotherapy performed only at the time of progression, seizure control at 1 year was better in the early radiotherapy group [21]. However, during the course of radiotherapy, seizures may occur for the first time or the frequency of seizures may increase, because radiotherapy leads to an acute inflammatory reaction, which can be associated with edema and increased intracranial pressure [8, 9]. In 2004, Bhansali et al. reported 11 patients with radiation-induced brain disorders [8]. Four of these patients (36%) had developed generalized seizures. In a review article published in 2007, seizures were reported to be symptoms of both acute radiation encephalopathy and late radiation-related necrosis [9]. However, no study has been available so far that evaluated the effect of irradiation to the brain on seizure activity during the course of radiotherapy for high-grade gliomas. However, these data would be very important in order to improve the monitoring and, if required, the anti-epileptic treatment of these patients. Therefore, the SURF-ROGG trial has been designed that will evaluate the seizure frequency during a course of radiotherapy for high-grade (grade III or IV) gliomas. Patients with low-grade (grade I or II) gliomas will not be included, because the treatment of these tumors and the dose-fractionation of radiotherapy are almost always different from the treatment of high-grade tumors [12].

In this trial, progression of seizure activity is defined as increase of seizure frequency by more than 50%, increase of severity of seizures (i.e. increase of generalized seizures by more than 50%), or initiation or increase of anti-epileptic medication by at least 25%. Evaluation of seizure activity is mainly based on patient-reported outcomes, i.e. on a seizure diary kept by the patients during the period of radiotherapy and up to 6 weeks following radiotherapy. Every day, the patients document the number and type of seizures, as well as the intake of anti-epileptic medication. At the end of radiotherapy, the patients are asked to complete a questionnaire regarding their satisfaction with the seizure diary. In addition to the patient-reported outcomes, EEG activity typical for epilepsy will be evaluated to receive also objective data.

If the SURF-ROGG trial shows an increase in seizure activity during the course of radiotherapy for high-grade gliomas, the findings of this trial may pave the way for a larger prospective trial and will likely contribute to closer patient monitoring and better anti-epileptic treatment.

## Data Availability

Not applicable, because no data have been generated until now. The trial was registered at clinicaltrials.gov (NCT04552756).

## Abbreviations

CTCAE: Common Terminology Criteria for Adverse Events
EEG: Electroencephalography
GCP: Good Clinical Practice
IDH: Isocitrate Dehydrogenase
MGMT: O^6^-Methyl-Guanine-DNA Methyl-Transferase
PCV: Procarbazine, Lomustine and Vincristine
QUANTEC: Quantitative Analyses of Normal Tissue Effects in the Clinic
SURF-ROGG: SeizURe Frequency during a Radiotherapy cOurse for high-Grade Gliomas
TMZ: Temozolomide
VMAT: Volumetric Modulated Arc Therapy
ZKS: Zentrum für Klinische Studien (Centre for Clinical Trials)
